### Study participants

A total of 800 participants are planned to be enrolled from May 19, 2019 to May 18, 2022. Patients with ≥3 renal cysts in both kidneys are eligible to be enrolled. Those who are not able to give informed consent or are pregnant will be excluded from enrollment. Cases of simple renal cysts and acquired cystic kidney disease that involve cyst formation as the result of renal failure will also be excluded from this study. However, patients with end-stage kidney disease who are receiving renal replacement therapy due to iCKD can be enrolled.

The patients will be classified into typical ADPKD, atypical polycystic kidney disease, and other iCKDs after enrollment. Typical ADPKD is defined according to Pei-Ravine criteria as previously described [17]. Atypical polycystic kidney disease is defined either when the case is typical ADPKD but the patient does not have a family history of polycystic kidney disease or when the imaging phenotype is atypical as follows: unilateral, asymmetric, segmental, lopsided, bilateral or unilateral atrophic kidneys [18]. Other iCKDs are rare disease entities in children and adolescents. The other iCKDs include but are not limited to the tuberous sclerosis complex, von Hippel-Lindau disease, ADTKD, ARPKD, *HNF-1β*-related disease and NPHP. Among the 800 participants, approximately 650 patients with typical ADPKD, 90 patients with atypical polycystic kidney disease, and 60 patients with other iCKDs will be enrolled.

The parents, siblings, or children of the enrolled patients are recommended to participate in the study by giving whole blood samples for a segregation study. We will collect family samples when genetic diagnosis is undetermined, genotype-phenotype severity is not matched, and when the extrarenal manifestation is severe. We will also collect family samples from the families with more than 3 affected individuals to define gene penetrance and modify gene effects.

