### Genetic pipeline

We will use a stepwise approach to confirm genetic diagnosis. First, we will use a targeted gene panel for the screening method. We designed a targeted gene panel (Twist Bioscience, San Francisco, CA, USA) encompassing 0.5 megabases, including 89 genes related to cystogenesis or ciliopathy as well as genes that are associated with extrarenal phenotypes such as liver cysts (Table 2). Twist technology has provided high-quality target enrichment probes to cover target genes uniformly and efficiently [25]. Targeted exon capture will be performed on genomic DNA samples using a Twist custom panel kit followed by 101 base paired-end sequencing on an Illumina NovaSeq6000 platform (Illumina, San Diego, CA, USA). Sequence reads will be aligned to the human reference genome (GRCh37/hg19) using BWA-MEM and further processed to call single nucleotide variants and indels following the GATK Best Practices workflow [26]. All variants covered by independent sequence reads with a depth of 8x or greater will be annotated with ANNOVAR. All variants will be visualized in silico to eliminate false positives. Additional genetic testing will be performed if the pathogenic mutations were not found using a targeted gene panel or if the patients have severe renal or extrarenal phenotypes compared to other family members. If the patients are clinically classified as having typical ADPKD but pathogenic mutations are not found using a targeted gene panel, the patients will undergo targeted resequencing with long-range polymerase chain reaction (PCR) combined with multiplex ligation-dependent probe amplification (MLPA) to detect large deletions. WES will take place in the following cases: 1) if the patients are clinically classified as typical ADPKD but no pathogenic mutations are found using a previous method, 2) if the patients are clinically classified as atypical polycystic kidney disease or other iCKD but pathogenic mutations are not found using a targeted gene panel, 3) if the patients present with a severe phenotype and variants cannot explain the severity, or 4) if the patients show extremely different phenotypes compared to other family members. Familial segregation analysis will also take place to define the pathogenicity of variants. A schematic representation of the genetic workflow is shown in Fig. 1.

**Table 2 Tab2:** Coverage of cystogenesis-related targeted gene panel

Target gene	Previously reported disease	Coverage
*AHI1*	Joubert syndrome	100%

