**Fig. 1 Fig1:**
[figure not shown]
Genetic analysis pipeline. A total of 800 probands with iCKD will be enrolled in the study. They will be classified into typical ADPKD, atypical polycystic kidney disease, or other/pediatric iCKDs. For the first screening genetic test, a targeted gene panel of 89 cytogenesis-related genes will be applied to the total population. All the variants will be analyzed by bioinformaticians to identify pathogenic mutations. For those with variants of undetermined significance (VUS) or no variants found by the gene panel, different genetic approaches will be taken for each class of iCKD. For those with typical ADPKD, targeted exome sequencing of *PKD1* after long-range PCR combined with MLPA will be performed to identify pathogenic mutations. If the mutations are not found by this method, WES will take place. For those with atypical polycystic kidney disease or pediatric iCKD, WES will be performed to identify pathogenic mutations. For the last step of genetic diagnosis, a family segregation study will be performed to elucidate the cause of genotype-phenotype discordance, in-family severity discordance, or discordance between renal and extrarenal manifestations. Abbreviations: ADPKD, autosomal dominant polycystic kidney disease; iCKD, inherited cystic kidney disease; PCR, polymerase chain reaction; MLPA, multiplex ligation-dependent probe amplification; PKD, polycystic kidney disease; VUS, variant of undetermined significance; WES, whole exome sequencing

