### Genotype-phenotype correlation analysis

Statistical analyses will be performed using a recent version of SPSS software (IBM Corp., Armonk, NY, USA). A linear regression model will be performed to identify the correlation between genotype and clinical parameters, including total kidney volume and estimated glomerular filtration rate. The cases will be classified into 5 classes using the Mayo imaging classification before analysis. The cases will also be classified into 6 groups according to the chronic kidney disease stages. Analysis of covariance, the Mann-Whitney test, and the chi-square test will be performed to compare variables between groups. The modifier effect of multiple genes on renal and extrarenal manifestations will also be assessed. A *P* value < 0.05 will be considered statistically significant.

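### Some whole exome sequencing and family testing is triggered by severity, so variants found or reclassified only that way can show false associations with severity

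*Protocol article*

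**What the plan says.** **Testing common to all.** According to the Fig. 1 legend, "a targeted gene panel of 89 cytogenesis-related genes will be applied to the total population".

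**Further testing of the proband (Genetic pipeline).** Additional testing follows a panel without a pathogenic mutation, "or if the patients have severe renal or extrarenal phenotypes compared to other family members". Four criteria lead to WES:

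1. "if the patients are clinically classified as typical ADPKD but no pathogenic mutations are found using a previous method"; for typical ADPKD, long-range PCR with MLPA comes first.
2. Atypical or other disease with a negative panel.
3. "if the patients present with a severe phenotype and variants cannot explain the severity".
4. "if the patients show extremely different phenotypes compared to other family members".

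**Family samples (Study participants).** "We will collect family samples when genetic diagnosis is undetermined, genotype-phenotype severity is not matched, and when the extrarenal manifestation is severe". Families with more than three affected members are sampled as well. Genetic pipeline says that segregation helps to decide whether a variant is pathogenic.

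**Analysis (Genotype-phenotype correlation analysis).** Total kidney volume and eGFR are related to genotype by linear regression, and groups are compared at P < 0.05. In addition, "The modifier effect of multiple genes on renal and extrarenal manifestations will also be assessed". The section does not say which variants enter these models or how a patient without WES is coded. Background names the search for modifier genes linked to severity as an aim of the study.

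**The concern.** The intensity of the search for variants depends partly on the outcome against which those variants are later tested. Criterion 3 works in one direction only: an unexplained severe course leads to WES, and no matching rule covers an unexplained mild one. The family trigger for severe extrarenal disease is also one-directional. Because segregation feeds the pathogenicity call, severity can influence both which variants are found and how they are classified.

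This is exposure ascertainment that differs by outcome. If an untested patient counts as a non-carrier, carriers of a variant visible only by WES are over-represented among severe patients even when the variant does nothing. A larger cohort does not remove this; it makes the false signal more significant. A modifier gene reported on that basis could not be told apart from an artefact of the search rule. The limitations in the Discussion cover the observational design, short follow-up and selection through hospitals, but not this.

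**Working it through.** The article gives no error rate, effect size or power for these analyses, so there is no figure to reproduce. The check asks what happens when the variant has **no** effect.

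**Inputs from the article**
- N = 800 (650 + 90 + 60), Study participants.
- α = 0.05, Genotype-phenotype correlation analysis; two-sided is assumed.
- 20% sequenced because the screen was negative, at any severity. Background gives about 20% without a causative mutation in typical ADPKD from earlier *PKD1*/*PKD2* sequencing. Carrying this over to the new panel and to all groups is an assumption.

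**Assumptions not in the article**
- Carrier frequency of a WES-only variant: f = 2%, 5%, 10%.
- Severe share: s = 10%, 20%, 30%.
- Share of severe patients sent to WES because of severity: w = 25%, 50%, 100%.
- Severity is standard normal and independent of the variant and of a negative screen.
- Patients without WES are coded as non-carriers.

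**Middle case by hand (f = 5%, s = 20%, w = 50%)**
- P(WES | severe) = 0.2 + 0.8 × 0.5 = 0.60; P(WES | not severe) = 0.20.
- Detected carriers: 0.05 × 0.60 = 3% of severe and 0.05 × 0.20 = 1% of non-severe patients. The true figure is 5% in both. The false odds ratio is (0.03/0.97)/(0.01/0.99) = 3.06.
- P(WES) = 0.2 × 0.60 + 0.8 × 0.20 = 0.28, so 800 × 0.05 × 0.28 = 11.2 detected carriers are expected.
- The top 20% of a standard normal has mean 0.280/0.2 = 1.40, the rest −0.280/0.8 = −0.35. Mean severity among those with WES is (0.12 × 1.40 − 0.16 × 0.35)/0.28 = 0.40.
- Mean of all others: −(0.014 × 0.40)/0.986 = −0.006. The false difference is 0.41 SD.
- Standard error ≈ √(1/11.2 + 1/788.8) = 0.30, so the expected z is 0.406/0.301 = 1.35. Rejection rate ≈ Φ(1.35 − 1.96) = 0.27.

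Simulation of the same case (2,000 runs, t-test on carrier status, equivalent to linear regression) gives 0.298 and 0.41 SD. The hand figure is slightly lower because it takes the variance as 1 in both groups.

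**Whole grid by simulation, N = 800**

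| Carrier frequency | False-positive rate over all s and w |
|---|---|
| 2% | 0.08–0.40 |
| 5% | 0.09–0.75 |
| 10% | 0.12–0.96 |

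The false difference is 0.16 to 0.66 SD, always towards greater severity in apparent carriers. With N = 650 and w = 50%, the rate is 0.10 to 0.52.

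**A trigger in both directions.** With f = 5%, the most extreme 20% (mild or severe) and all of them sequenced, the mean difference is about 0, but the rejection rate is still 0.16. The one-directional counterpart gives 0.64.

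**Checks on remedies, same null data, N = 800**
- Variants assayed in everyone: 0.044–0.063.
- Only patients who had WES: 0.040–0.055.
- Only patients sequenced because the screen was negative: 0.038–0.059.

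Reclassification through selective segregation was not simulated. The argument for it is qualitative.

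**The case against.** The strongest reply is that the decisive step is not in the article. False associations of this kind need two things: variants visible only through selective testing must enter the models, and untested patients must be coded as non-carriers. The article states neither, and the handling of missing genotypes is commonly left to an analysis plan that is not shown. This stands, and it limits the conclusion to what *can* happen.

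A reader might infer that the genotype-severity and modifier analyses as a whole will yield false findings. The documents do not support that. The panel is run in everyone and includes *PKD1*, *PKD2*, *GANAB*, *DNAJB11* and the polycystic liver genes, and the Discussion presents it as a means to explain differing extrarenal disease. Detection of these variants does not depend on severity; only their classification could, through selective segregation.

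A reader might also infer that mild panel-positive patients never get WES or family testing and that severe ones always get both. That is not what the text says:
- Criterion 4 and the severity-mismatch trigger have no stated direction and can admit unusually mild patients.
- Criterion 3 also requires that the variants found do not explain the severity.
- Families with more than three affected members are sampled whatever the severity.
- Criteria 1 and 2 do not refer to severity.

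Family testing, moreover, is not a deeper search of the proband; it bears on how a variant is classified.

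What remains is that the testing rule itself is fixed in this document. If a mild panel-positive patient was never sequenced, no later analysis plan can recover that genotype. It can only limit which results are used, and the article states no such limit.

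**Conclusion.** The point holds in limited form. Some triggers for WES and family testing depend on severity, and severity is the outcome of the analyses. Variants found only by such WES, or reclassified only through such segregation, can show false associations if they enter the models with untested patients as non-carriers.

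The size is illustrative. Every setting examined was inflated, but carrier frequency, severe share and WES uptake are all assumed. The upper end needs 10% carriers, 30% severe and every severe patient sequenced, which the second condition in criterion 3 makes unlikely. The 20% screen-negative share comes from earlier sequencing, not from this pipeline. In typical ADPKD, WES follows only after long-range PCR and MLPA have also failed, so the share sequenced for that reason may be smaller and the contrast larger.

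**What to change.** Add to Genotype-phenotype correlation analysis:

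1. The primary genotype-severity and modifier models use variants called by the targeted panel, classified without information from severity-triggered testing. Long-range PCR and MLPA results triggered only by a negative screen may stay for the *PKD1*/*PKD2* genotype.
2. WES-only variants are missing, not absent, in patients without WES. They are tested only among patients sequenced for severity-independent reasons (criteria 1 and 2).
3. Variants found through severity-triggered WES, or reclassified through severity-triggered segregation, are reported as diagnostic or hypothesis-generating.

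This changes wording only. The testing rules stay as they are and no new sequencing is needed. The price is that modifiers discovered through severity-triggered WES cannot be claimed as tested associations, and that WES-based tests have fewer patients. At an assumed 20%, that is 0.20 × 800 = 160 patients, with 0.05 × 160 = 8 carriers of a 5% variant.

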**Fig. 1 Fig1:**
[figure not shown]
Genetic analysis pipeline. A total of 800 probands with iCKD will be enrolled in the study. They will be classified into typical ADPKD, atypical polycystic kidney disease, or other/pediatric iCKDs. For the first screening genetic test, a targeted gene panel of 89 cytogenesis-related genes will be applied to the total population. All the variants will be analyzed by bioinformaticians to identify pathogenic mutations. For those with variants of undetermined significance (VUS) or no variants found by the gene panel, different genetic approaches will be taken for each class of iCKD. For those with typical ADPKD, targeted exome sequencing of *PKD1* after long-range PCR combined with MLPA will be performed to identify pathogenic mutations. If the mutations are not found by this method, WES will take place. For those with atypical polycystic kidney disease or pediatric iCKD, WES will be performed to identify pathogenic mutations. For the last step of genetic diagnosis, a family segregation study will be performed to elucidate the cause of genotype-phenotype discordance, in-family severity discordance, or discordance between renal and extrarenal manifestations. Abbreviations: ADPKD, autosomal dominant polycystic kidney disease; iCKD, inherited cystic kidney disease; PCR, polymerase chain reaction; MLPA, multiplex ligation-dependent probe amplification; PKD, polycystic kidney disease; VUS, variant of undetermined significance; WES, whole exome sequencing

### Genotype-phenotype correlation analysis

Statistical analyses will be performed using a recent version of SPSS software (IBM Corp., Armonk, NY, USA). A linear regression model will be performed to identify the correlation between genotype and clinical parameters, including total kidney volume and estimated glomerular filtration rate. The cases will be classified into 5 classes using the Mayo imaging classification before analysis. The cases will also be classified into 6 groups according to the chronic kidney disease stages. Analysis of covariance, the Mann-Whitney test, and the chi-square test will be performed to compare variables between groups. The modifier effect of multiple genes on renal and extrarenal manifestations will also be assessed. A *P* value < 0.05 will be considered statistically significant.

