Moreover, the exact methods and pipelines to find genetic mutations in iCKDs are not clear at this point. It may be reasonable to perform targeted exome sequencing or Sanger sequencing of *PKD1* and *PKD2* to define pathogenic mutations in well-known clinical phenotypes such as ADPKD. However, our previous study demonstrated that approximately 20% of patients with typical ADPKD did not reveal causative germline mutations by targeted exome sequencing of *PKD1* and *PKD2* [11]. In addition, extrarenal manifestations often do not follow renal manifestations. For example, the severity of polycystic liver accompanying ADPKD does not always correlate with the severity of renal disease [12]. Therefore, modifying genetic effects or gene dosage effects may play a role in determining the severity of renal and extrarenal phenotypes in ADPKD [13]. In addition, apart from typical ADPKD, there are patients with atypical polycystic kidney disease who either do not show concordant features within the family, do not have typical imaging features of ADPKD, or have discordant disease severity between renal volume and renal function [14]. Mutations in *GANAB* and *DNAJB11* are known to cause a mild phenotype of polycystic kidney and liver disease [15, 16]. However, the exact prevalence and prognosis of atypical polycystic kidney disease is unknown at this point. Last, iCKDs in the pediatric population are typically rare diseases, and their molecular diagnoses are even more difficult. Therefore, building a cohort of iCKDs is necessary to reveal their genetic characteristics.

Therefore, we designed a 3-year prospective, multicenter, cohort study to establish a cohort of Korean iCKD patients, establish a customized genetic analysis pipeline that can genotype each iCKD and identify the modifying genes associated with the severity of the disease phenotype.

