Since the clinical diagnosis of iCKD is not always easy, genetic characterization will help to confirm the diagnosis of each iCKD case and to elucidate the heterogeneity of disease manifestations within the family. Since there are over 100 genes that can result in ciliopathies, Sanger sequencing or targeted exome sequencing of a few genes can be time-consuming and costly. The targeted gene panel approach through parallel sequencing of targeted subsets of disease-specific genes may be an effective screening method for iCKD cases. Recent papers have also reported the effectiveness of gene panels and subsequent WES approaches in confirming genetic diagnosis [10, 31, 32]. Therefore, we designed a targeted gene panel for the initial screening method to find causal variants. The gene panel can be designed and customized for research purposes. We included 13 genes associated with Joubert syndrome, 27 genes associated with polycystic liver, 8 genes associated with ADPKD, 1 gene associated with ARPKD, 11 genes associated with NPHP, 3 genes associated with Alport syndrome, 2 genes associated with ADTKD, 2 genes associated with tuberous sclerosis complex and 19 other ciliopathy-related genes in our targeted gene panel. The composition of the gene panel will help us not only identify causal variants for renal cystic disease but also explain the heterogeneity of extrarenal manifestations in the same disease.

Patient recruitment from secondary and tertiary hospitals across the country will represent the Korean cohort of iCKDs. The sample size of 800 should provide sufficient statistical power to address the heterogeneity of typical ADPKD, atypical polycystic kidney disease, and pediatric iCKDs. In particular, the establishment of a pediatric iCKD subcohort and atypical polycystic kidney disease cohort can be helpful in defining pathogenic mutations in each group because they are so rare, and genetic diagnosis of each case can be difficult without building a multicenter cohort. The five well-organized study teams (research team, statistical analysis team, database team, sequencing and biobanking team, and genetic analysis team) of this study will facilitate the study process. Various other factors, such as central electronic case report forms, researcher meetings, study nurse meetings, comprehensive study analyses and regular monitoring, will keep the quality of this study as high as possible.

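### An unadjusted P < 0.05 is the only significance rule for a modifier-gene search of unstated size, with a false-positive risk of about 40% for 10 genes and 99% for the full panel

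*Protocol article*

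**What the plan says.** The Background of the protocol article gives three aims: to build the cohort, to set up a genotyping pipeline, and to "identify the modifying genes associated with the severity of the disease phenotype".

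The section Genotype-phenotype correlation analysis plans linear regression of genotype on "clinical parameters, including total kidney volume and estimated glomerular filtration rate". It classifies cases into five Mayo imaging classes and six chronic kidney disease groups, and names three methods for comparing groups. It then states: "The modifier effect of multiple genes on renal and extrarenal manifestations will also be assessed". The next sentence sets the threshold, a P "value < 0.05 will be considered statistically significant". The article contains no other significance rule. It mentions no multiplicity adjustment, false discovery rate, statistical replication step, shortlist of candidate modifiers or exploratory label.

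On the gene set, the section Genetic pipeline describes a panel "including 89 genes related to cystogenesis or ciliopathy", and the legend to Fig. 1 says "a targeted gene panel of 89 cytogenesis-related genes will be applied to the total population". The Discussion expects the panel's composition to "also explain the heterogeneity of extrarenal manifestations in the same disease". Its breakdown by disease, which ends with "2 genes associated with tuberous sclerosis complex and 19 other ciliopathy-related genes in our targeted gene panel", does not add up to 89.

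**The concern.** A 5% threshold limits the error of a single test. Applied gene by gene in a search, it lets false findings accumulate with the number of genes and phenotypes. Because naming modifier genes is an aim, each gene that crosses the threshold may be reported as a result. The article's closing summary links the study to precision medicine, so a false modifier could be carried forward.

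The threshold is written into the plan and sits next to the modifier assessment. The criticism is therefore of a stated rule and what follows if it is applied, not of a detail that the article has left out.

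**Working it through.** The plan gives no family-wise error rate and no number of tests, so there is no figure of its own to reproduce. The check asks what the stated rule implies over a range of search sizes.

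**Inputs**
- Level per test: 0.05 (Genotype-phenotype correlation analysis).
- Genes: only described as multiple. The ranges below are assumptions. The Discussion counts 27 polycystic-liver genes, which gives one plausible subset. The full panel is 86 or 89.
- Phenotypes: at least total kidney volume and eGFR, plus extrarenal manifestations.
- Participants: about 650 with typical ADPKD (Study participants), used in the simulation only.

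**Panel size.** Genetic pipeline and the Fig. 1 legend say 89. Table 2 lists 86 genes. The Discussion's breakdown is 13 + 27 + 8 + 1 + 11 + 3 + 2 + 2 + 19 = 86.

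**Formulas**, for m independent tests with no true effect:
- P(at least one false positive) = 1 − 0.95^m
- Expected false positives = 0.05 × m

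| Search | m | P(at least one) | Expected |
|---|---|---|---|
| 10 genes, one phenotype | 10 | 0.401 | 0.5 |
| 20 genes, one phenotype | 20 | 0.642 | 1.0 |
| 27 genes, one phenotype | 27 | 0.750 | 1.35 |
| 86 genes, one phenotype | 86 | 0.988 | 4.3 |
| 89 genes, one phenotype | 89 | 0.990 | 4.45 |
| 86 genes, two phenotypes | 172 | 0.9999 | 8.6 |
| 89 genes, two phenotypes | 178 | 0.9999 | 8.9 |

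The probability first reaches 90% at 45 tests and 95% at 59.

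**Sensitivity to correlated phenotypes.** Kidney volume and eGFR will be correlated, so independence across them is optimistic arithmetic. A null simulation used n = 650, two phenotypes with correlation 0, 0.5 or 0.9, and an assumed carrier frequency of 1% or 5% per gene, with 1,000 replicates per setting.
- 89 genes: at least one false modifier in 99.8% of replicates or more, with about 6 to 9 genes falsely flagged on average.
- 20 genes: 75% to 88%.
- 10 genes: 50% to 66%.

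Correlation between the phenotypes reduces the count but does not bring the error near 5%.

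**Under a corrected threshold.** Bonferroni over 86 genes and two phenotypes gives 0.05/172 = 0.00029, and over 89 genes 0.05/178 = 0.00028. For one phenotype the values are 0.05/86 = 0.00058 and 0.05/89 = 0.00056. The family-wise error under independence is then 0.049 in each case.

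**The case against.** The strongest reply is that the article never says every panel gene will be tested as a modifier. It gives no number of genes, no unit of analysis and no specific test. This stands. A reader might infer that false modifier genes are virtually certain, but that holds only for a search of roughly panel size in which nearly all genes are null and each has enough carriers to test. The panel-wide reading is reasonable: the panel is the only gene set applied to all participants, no shorter list is given, and the Discussion expects the panel to account for extrarenal heterogeneity. It is still an inference, so the result has to be given as a range.

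A reader might also infer that the study could not tell real modifiers from noise. The documents do not support that. Families with more than three affected members are sampled partly to study modifier effects, and segregation analysis follows where severity is discordant. These are further lines of evidence, and they are not described as P < 0.05 screens.

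It is tempting to add error from all pairwise comparisons among Mayo classes and kidney disease stages. The plan does not state such comparisons. The named methods include ones that can serve as single overall tests, and pairwise tests that share groups are not independent. Nor does the plan say that both kidney-volume methods, or exome data from selected patients, will each feed a separate modifier search.

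Finally, a statistical analysis plan that is not shown may add an adjustment, and an article need not spell one out. The absence of a named primary contrast is therefore not criticised in itself. What remains open to criticism is that the published rule, followed as written, is unadjusted.

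**Conclusion.** The point holds in bounded form. The stated rule gives a chance of at least one false modifier of about 40% for 10 genes and 75% for 27, rising to about 99% for the full panel, on one phenotype. Over the full panel, about 4 false positives are expected with one phenotype and about 9 with two. Even the smallest of these searches has about eight times the nominal 5% (0.401/0.05).

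The table assumes independent tests and no true modifier among the genes tested. The simulation relaxes independence between phenotypes, but not between genes. The number of genes tested is an assumption throughout.

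The 89 versus 86 discrepancy is a real inconsistency in the description of the panel. It is not a misstated number of tests, because the article states none, and it moves the one-phenotype probability only from 0.988 to 0.990. It matters for setting a corrected threshold.

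The aims of building the cohort and the diagnostic pipeline do not depend on this threshold. The modifier-gene aim does.

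**What to change.** Before analysis, replace the single threshold with a graded rule:

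1. Keep 0.05 for one named primary genotype contrast and one named severity outcome.
2. State which genes and phenotypes make up the modifier search. Judge those tests under a 5% false discovery rate, or use Bonferroni over the genes × phenotypes actually tested (for example 0.05/172 = 0.00029 for 86 genes and two phenotypes).
3. Label the remaining comparisons by imaging class, by kidney disease stage and from exome sequencing as exploratory, and report them with confidence intervals.
4. Reconcile the panel count between Genetic pipeline and Fig. 1 (89) and Table 2 and the Discussion (86).

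This changes analysis wording only, with no new participants, samples or sequencing. The price is that fewer modifier genes will be called significant, and modest true effects may miss the stricter threshold. A false discovery rate is usually the less severe of the two options in that respect.
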